## Abstract

**Background:**

Despite numerous pharmacological treatments, individuals with schizophrenia continue to exhibit significant residual cognitive impairments, adversely affecting the progression of the illness and their overall quality of life. Preliminary evidence indicates that transcranial direct current stimulation (tDCS) and music therapy (MT) may offer potential benefits for enhancing cognitive function in schizophrenia. This study aims to examine the synergistic efficacy of tDCS and MT on cognitive impairments in individuals with schizophrenia and to elucidate the potential mechanisms involved in this process.

**Methods:**

The study is designed as a randomized, double-blind, sham-controlled trial. All patients with schizophrenia will be randomly assigned to one of five groups: active tDCS combined with MT group, sham tDCS combined with MT group, active tDCS group, MT group, and a control group. The anodal electrode of tDCS will be positioned over the medial prefrontal cortex (mPFC), while the cathodal electrode will be placed over the visual cortex. MT will incorporate both Western Mozart and traditional Chinese classical music. The protocol involves 30-minute sessions conducted once daily, 5 days per week, for 4 consecutive weeks. The primary outcome measure is change in cognitive function, secondary outcomes include changes in psychotic symptoms, social function, and quality of life. Assessments will be evaluated at baseline (T0), after 2 weeks (T1), and after 4 weeks (T2). Furthermore, we will employ functional near-infrared spectroscopy (fNIRS) to examine hemodynamic changes on the cerebral cortex, and explore the neural effects of this combined treatment approach.

**Discussion:**

This study proposes an innovative non-pharmacological treatment protocol that combines tDCS targeting the mPFC with MT to improve cognitive impairments in schizophrenia. As a proof-of-concept study, it aims to provide empirical evidence for the effectiveness of this combined intervention. Moreover, this study seeks to elucidate the underlying neural mechanisms and offer a rigorous framework for future clinical trials, ultimately providing a novel therapeutic strategy for enhancing cognitive functions in patients with schizophrenia.

**Clinical trial registration:**

https://www.chictr.org.cn/, identifier, ChiCTR2400093161

**Trial registration details:**

The study is registered with https://www.chictr.org.cn/ under protocol registration number ChiCTR2400093161 (date of registration: 29. November. 2024). It was approved by the Research Ethics Committee of the Second Affiliated Hospital of Xinxiang Medical University (Approval Code: XYEFYLL-2024-82, Approval Date: 6 November 2024). Recruitment began in December 2024.

## Background

Schizophrenia is a severe and chronic psychiatric disorder with a lifetime prevalence of approximately 1% (1). It is characterized by positive symptoms, negative symptoms, and cognitive impairments such as deficits in working memory, verbal learning, attention, processing speed, and social cognition (2, 3). As a core symptom of schizophrenia, cognitive impairments typically manifest early in the disease course and may persist, significantly impacting patients’ social functioning and daily living abilities (4, 5). These cognitive impairments associated with schizophrenia (CIAS) encompass deficits in working memory, verbal learning, attention, processing speed, and social cognition (4, 5). Deficits in working memory and executive functions can hinder patients’ ability to plan, organize, and complete tasks, while impairments in social cognition may lead to difficulties in interpersonal relationships (6–8). Despite adequate pharmacological treatment, approximately 30% of individuals with schizophrenia persist in exhibiting cognitive impairments. Additionally, pharmacological treatments are often associated with substantial financial burdens for families, low compliance, and potential adverse effects, including extrapyramidal symptoms, endocrine, and metabolic disturbances (6). Consequently, the development of effective non-pharmacological alternatives for cognitive impairments is a major research priority.

Transcranial direct current stimulation (tDCS) is proposed as a noninvasive neuromodulatory strategy for schizophrenia due to its cost-effective, minimal adverse effects, and affordability (7). tDCS employs a constant, low-intensity direct current to modulate neuronal activity in the cerebral cortex (8). The potential mechanism involves changes in the resting membrane potential induced by hyperpolarization or depolarization depending on the polarity of the stimulation. Currently, tDCS predominantly targets the left dorsolateral prefrontal cortex (DLPFC) as the anodal site in schizophrenia research (9). The application of tDCS in individuals with schizophrenia typically involves positioning the anode on the left DLPFC, with the cathode placed either over the right supraorbital region or on the right DLPFC (10, 11). Notably, tDCS can modulate neural activity and enhance neuroplasticity, which can result in improvements in working memory, attention, and social cognitive abilities in patients with schizophrenia (12–15). A meta-analysis has demonstrated a significant positive impact of prefrontal tDCS on working memory, with a medium effect size (16).

Evidence from electroencephalogram, neuroimaging, and neuromodulation research has identified that the medial prefrontal cortex (mPFC) as a critical region implicated in cognitive dysfunction associated with schizophrenia (9, 17). Consequently, tDCS targeting the mPFC has the potential to enhance cognitive functions, including working memory, decision-making, and problem-solving (18). Although tDCS has shown promising results for the treatment of schizophrenia, recent studies indicate that its efficacy may be further enhanced when combined with other strategies (7).

Music therapy (MT) has been substantiated as a non-pharmacological treatment option for schizophrenia (19). MT is categorized into two forms: active MT, which encompasses activities such as singing, playing instruments, and music creation, and passive MT, which involves music listening (20). Its non-invasive nature, cost-effectiveness, and favorable tolerability make it a compelling adjunctive treatment for symptom management in schizophrenia. A systematic review including 13 randomized controlled trials with a total of 1,114 schizophrenia patients demonstrated improvements in cognitive functions, quality of life, social interest, and overall functioning after MT (19). MT has the potential to enhance cognitive functions and emotional states by facilitating the synchronization of activities across multiple brain regions and neural circuits (21). This effect has been observed in the mPFC, hippocampus, amygdala, insula, cingulate cortex, and hypothalamus (22). Consequently, MT may serve as a valuable adjunctive treatment for schizophrenia, particularly in alleviating cognitive deficits and promoting overall well-being through its synergistic effects (23).

Furthermore, the integration of tDCS with MT may yield greater cognitive improvements compared to the application of either treatment in isolation. tDCS has demonstrated efficacy in enhancing cognitive functions, especially in the mPFC, which is crucial for working memory, executive function, and self-referential cognition (17). The emotional and motivational enhancement effects associated with MT may enhance patient engagement and compliance with tDCS treatment, while tDCS may potentiate the effects of MT on brain functions (24). Based on this, we hypothesize that this integrated approach both targeting the mPFC may provide a novel therapeutic option for schizophrenia. Despite the growing body of literature on tDCS or MT, investigations into their combined application for the treatment of schizophrenia remain limited. Furthermore, clinicians and researchers have been explored objective assessment methodologies, particularly through neuroimaging techniques. Functional near-infrared spectroscopy (fNIRS) is an objective, portable, and cost-effective approach for evaluating cortical activity by monitoring blood oxygenation changes (25). Multichannel fNIRS instruments facilitate the measurement of alterations in specific brain regions and their temporal interrelationships (26). To date, no research has investigated the synergistic effects of tDCS and MT on cognitive impairments, nor the potential mechanisms underlying their combined application in schizophrenia.

This study protocol proposes a non-pharmacological approach by integrating tDCS with MT to investigate their synergistic effects on cognitive impairments in individuals with schizophrenia.This proof-of-concept study has three overall objectives. The first objective is to assess the efficacy of tDCS combined with MT on the treatment of cognitive impairments in patients with schizophrenia. We hypothesize that the integration of tDCS with MT will demonstrate greater effectiveness in ameliorating cognitive impairments compared to the application of either MT or tDCS. The second objective is to evaluate the efficacy of this integrated treatment approach on the positive and negative symptoms, as well as the quality of life, and social functioning. We expect that tDCS combined with MT will ameliorate both positive and negative symptoms and enhance overall functioning. The third objective is to investigate hemodynamic changes in the brain and explore the neural mechanisms involved in this combined treatment process by utilizing fNIRS during verbal fluency tasks (VFT). We propose the hypothesis that combined treatment will ameliorate prefrontal dysfunction, as measured by fNIRS, with more pronounced improvements observed in the combined group compared to those receiving tDCS or MT alone.

## Method

### Study design

This is a prospective, single-center, randomized, double-blind, sham-controlled study designed to assess the effects of tDCS combined with MT on the improvement of cognitive functions in patients with schizophrenia. Eligible participants will be recruited and randomly allocated into five groups in equal proportions (1:1:1:1:1): active tDCS combined with MT group (Group 1), sham tDCS combined with MT group (Group 2), active tDCS group (Group 3), MT group (Group 4), and control group (Group 5). Assessments will be conducted at baseline (T0), after 2 weeks (T1), and after 4 weeks (T2). The study design is depicted in **Figure 1**.

**Figure 1 f1:**
[figure not shown]
Flowchart of the study design. This flowchart outlines the various stages of the study as well as the corresponding group assignments. The table provides a detailed list of the assessments conducted at different time points. BPRS, Brief Psychiatric Rating Scale; CGI, Clinical Global Impressions; fNIRS, Functional Near-Infrared Spectroscopy; MCCB, MATRICS Consensus Cognitive Battery; MT, music therapy; PANSS, Positive and Negative Syndrome Scale; SDSS, Social Dysfunction Screening Scale; SQLS, Schizophrenia Quality of Life Scale.

### Recruitment

Participants will be recruited from the Department of Psychiatry, the Second Affiliated Hospital of Xinxiang Medical University. The trial will be advertised via the hospital’s official website and various media platforms. Additionally, informational leaflets will be distributed within the Department of Psychiatry, and psychiatrists will provide an overview of the study’s content. Potential participants will receive both oral and written information regarding the study’s procedures as well as its potential benefits and risks. All participants and their legal guardians will sign the informed consent document. Detailed written informed consent is provided in **Supplementary Material**. In accordance with the Declaration of Helsinki’s Ethical Principles of Medical Research Involving Human Subjects, the study was approved by the Research Ethics Committee of the Second Affiliated Hospital of Xinxiang Medical University (Approval Number: XYEFYLL-2024-82, Approval Date: 6 November 2024) and registered with the China Clinical Trials Center (Registration Number: ChiCTR2400093161). The trial will be conducted at the Second Affiliated Hospital of Xinxiang Medical University. This study protocol is in accordance with the 2013 Standard Protocol Items: Recommendations for Interventional Trials (SPIRIT) statement guideline (27).

### Eligibility criteria

Participants will be assessed based on the inclusion and exclusion criteria detailed in **Table 1**. All patients routinely undergo the Drug Abuse Screening Test (DAST-10) and the Alcohol Use Disorders Identification Test (AUDIT) at admission, which are standard procedures at our hospital. During the enrollment, we will assess drug and alcohol abuse by reviewing the standardized test results and medical records of patients at admission. Severe drug and alcohol dependence, defined as a score of ≥3 on the DAST-10 (28) or ≥8 on the AUDIT (29) will be excluded from the study. The study will be discontinued under the following conditions: (1) the emergence of urgent medical issues; (2) the occurrence of serious adverse events and side effects; or (3) the participant or their family members express unwillingness to continue participation in the trial. Participants had been on a stable dose of antipsychotic medication for a minimum of two weeks, before the trial began. These medication doses remained unchanged throughout the study.

**Table 1 T1:** Inclusion and exclusion criteria.

Inclusion criteria
1. Meets the clinical diagnostic criteria for schizophrenia according to DSM-5 for the current episode.
2. Patients who achieve a stable period through oral antipsychotic drug treatment are defined by the following criteria: a score of ≤5 on the items of delusion, hallucinatory behavior, exaggeration, and suspiciousness/victimization in the Positive and Negative Symptom Scale (PANSS), and a score of ≤4 on the PANSS conceptual disorganization.
3. Currently undergoing treatment with atypical antipsychotic medications, with equivalent doses of antipsychotic drugs calculated using the defined daily dose method.
4. Han ethnicity.
5. Ages between 18-55 years.
6. Normal hearing.
Exclusion criteria
1. Presence of brain organic lesions, intellectual disability, or other physical illnesses.
2. Frequent or persistent migraines.
3. Metal in skull and pacemaker.
4. Currently having epilepsy or a family history of epilepsy and other mental illnesses.
5. Severe drug and alcohol dependence.
6. Pregnant or lactating women.
7. Currently undergoing other neurostimulation therapy or evidence-based psychotherapy.

DSM-5: Diagnostic and Statistical Manual of Mental Disorders, 5th edition; PANSS, Positive and Negative Syndrome Scale.

### Randomization

The experiment will be conducted by an independent statistician, who was otherwise not involved in the study, utilizing random number tables to randomize the allocation of participants into one of five groups labeled ‘1, 2, 3, 4, 5.’ Specifically, these groups are coded as follows: active tDCS combined with MT (label = 1), sham tDCS combined with MT (label = 2), active tDCS alone (label = 3), MT alone (label = 4), and a control group (label = 5).

The randomization process was conducted using Microsoft Excel 2019. First, the 60 eligible patients were assigned unique identification numbers ranging from 1 to 60. Each number was then associated with a random value generated using the “=RAND ()” function in Excel. To ensure the random values remained fixed, the “Paste Special” function was used to convert the random values into static numbers. Subsequently, the list of patient numbers was sorted in descending order based on the generated random values. Following this sorting, the patients were sequentially allocated into five groups (Group 1 to Group 5), with 12 patients in each group, based on their order in the sorted list. This method ensured a completely random allocation of patients into the five study groups.

### Blinding

All participants and the psychiatrists conducting the assessments will remain blinded during the study. Regarding the implementation of blinding procedures, we have established the following considerations and measures. The specific group assignments of patients will be disclosed exclusively to the principal investigator. Furthermore, five distinct groups will be engaged to execute the treatment, with stringent restrictions in place to prevent inter-team communication concerning the details of their respective treatment. Each group will be informed solely of its own treatment plan and will remain unaware of both the specific group assignments and the plans of the other teams. During the experiment, the principal investigator will provide each group with the designated measures. Subsequently, each team will implement the experimental treatments on their respective patient cohorts. Patients remain blinded to the sequence allocation and are instructed to refrain from discussing group assignments, the treatments received, questionnaire completion, or any other elements of the experimental protocol among themselves. During the outcome measurement phase, personnel tasked with data collection and analysis are also blinded to the group assignments and specific measures. Next, the principal investigator will perform two unblinding procedures, one prior to and one following the data analysis. The initial unblinding will occur post data-lock, categorizing the data into Groups 1-5 without disclosing the actual alignment with Groups 1, 2, 3, 4, and 5, or their true group assignments. The second unblinding will be conducted after the completion of data analysis, elucidating the specific group identities corresponding to Groups 1, 2, 3, 4, and 5.

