### Music therapy

For music selection, we will select western Mozart and Chinese classical music based on previous research (19, 30). For Western music, we will select Mozart’s Sonata K.448, a choice based on relevant literature that demonstrating its positive effects on improving symptoms in patients with schizophrenia (30). For traditional Chinese classical music, Pingsha Luoyan (Wild Geese Descending on the Sandbank), Chunjiang Huayueye (Moonlit River in Spring), Gaoshan Liushui (High Mountains and Flowing Water), and Shimian Maifu (Ambush from Ten Sides) will be selected according to a previous study by Lam et al. (19). For details, see **Table 2**. Participants in Group 1 (active tDCS combined with MT group), Group 2 (sham tDCS combined with MT group), and Group 4 (MT group) will engage in 20 sessions, each lasting 30 minutes, conducted once daily, five days per week over a four-week period. Notably, tDCS and MT will be conducted simultaneously in the Group 1 and Group 2. To minimize the potential confounding effects of temporal variables across the four groups (Groups 1, 2, 3, and 4), each treatment will be conducted within the same time period on the same day, with consistent start and end times. Participants in the control group (Group 5) will continue their regular medication treatment without receiving tDCS or MT. The detailed experimental design and operational procedures, please see to **Figure 2**.

**Table 2 T2:** The standardize arrangement for music intervention.

Session	Music Category	Music Title
1	Western Mozart	Mozart’s sonata K.448
2	Chinese classical music	Pingsha Luoyan
3	Western Mozart	Mozart’s sonata K.448
4	Chinese classical music	Chunjiang Huayue Ye
5	Western Mozart	Mozart’s sonata K.448
6	Chinese classical music	Gaoshan Liushui
7	Western Mozart	Mozart’s sonata K.448
8	Chinese classical music	Simian Maifu
9	Western Mozart	Mozart’s sonata K.448
10	Chinese classical music	Erquan Yingyue
11	Western Mozart	Mozart’s sonata K.448
12	Chinese classical music	Zuiyu Changwan
13	Western Mozart	Mozart’s sonata K.448
14	Chinese classical music	Youlan
15	Western Mozart	Mozart’s sonata K.448
16	Chinese classical music	Saishang Qu
17	Western Mozart	Mozart’s sonata K.448
18	Chinese classical music	Xiyang Xiaogu
19	Western Mozart	Mozart’s sonata K.448
20	Chinese classical music	Meihua Sannong

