### Auditing

The Principal Investigator will checked the CRFs and completed pro formas on a weekly basis. Research records in both paper and digital forms will be checked every two weeks for accuracy, and any discrepancies will be noted, discussed, and corrected.

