## Discussion

To the best of our knowledge, this represents the first randomized, double-blind, sham-controlled trial designed to assess the synergistic effects of tDCS and MT on cognitive impairments in patients with stable schizophrenia. Cognitive impairment constitutes a core symptom that substantially impacts the quality of life and social functioning of patients. In this context, we present an innovative study protocol to investigate the potential for cognitive improvement in schizophrenia through the combination of tDCS and MT. We hypothesize that the group receiving both active tDCS and MT will exhibit more pronounced effects compared to those receiving either tDCS or MT alone. If our hypothesis is validated, this study will offer an effective therapeutic strategy of cognitive impairments, thereby aiding clinical psychiatrists and potentially improving patients’ quality of life and social functioning. Considering the tDCS might be widely accessible for home use and the existing evidence supporting the efficacy of MT, this combination appears to be a promising approach for translational application in clinical practice. The implementation of this strategy could yield substantial clinical and economic benefits in the treatment of schizophrenia. This study will provide important references for future larger-scale clinical trials and is expected to promote the widespread application of combined tDCS and MT in clinical practice.

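### The plan says all participants are blinded, but only Group 1 versus Group 2 is sham-controlled; patients in Groups 3, 4 and 5 can tell what they do not receive

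*Protocol article*

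**What the plan says.** All references are to the protocol article.

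- **Label.** Study design: "This is a prospective, single-center, randomized, double-blind, sham-controlled study". The Abstract and the Discussion repeat the double-blind and sham-controlled description.
- **Who is blinded.** Blinding: "All participants and the psychiatrists conducting the assessments will remain blinded during the study". For participants the measures are non-disclosure of allocation, separate treatment teams, and an instruction not to talk about treatment.
- **Arms.** Randomization gives the last three labels as "active tDCS alone (label = 3), MT alone (label = 4), and a control group (label = 5". Sham tDCS is used only in Group 2, together with music. No sham music is described.
- **Control.** Music therapy: "Participants in the control group (Group 5) will continue their regular medication treatment without receiving tDCS or MT".
- **Hypotheses.** The Background expects the combination to do better than either MT or tDCS on cognition, and better than tDCS or MT alone on fNIRS. The Discussion expects that "the group receiving both active tDCS and MT will exhibit more pronounced effects compared to those receiving either tDCS or MT alone".
- **Teams.** Blinding: "Furthermore, five distinct groups will be engaged to execute the treatment". Each team knows its own treatment plan and not those of the others.
- **Allocation key.** Blinding gives the group assignments to the principal investigator only. Date management makes that role one of two with access to the CRFs. Auditing adds: "The Principal Investigator will checked the CRFs and completed pro formas on a weekly basis".

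**The concern.** Whether a device is fitted, whether music is played and whether there are sessions at all are plain to the patient. Keeping the allocation label secret does not hide them. The statement about all participants is therefore a property that the design, as described, lacks.

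This matters because the hypotheses lean on the open comparisons. Group 1 and Group 4 differ by the current, by the experience and expectation of wearing a device, and by the team. If Group 1 did better, the trial's label would present the result as double-blind, sham-controlled evidence for the combination. The primary outcome, the MCCB, is a performance battery and depends on effort. Blinded raters therefore do not fully remove participant expectancy, and they offer less protection still for the patient's own view of quality of life.

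Two further arrangements weaken even the good contrast. With one team per arm, any difference between teams is also a difference between arms. And the one role that knows the allocation also reviews the outcome records.

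**Working it through.** **1. What each patient can perceive** (Study design, Randomization, tDCS and Music therapy sections)

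| Group | Device | Music | Evident to the patient |
|---|---|---|---|
| 1 | active | yes | neither component missing |
| 2 | sham | yes | neither component missing |
| 3 | active | no | no music; perhaps not whether the current is active |
| 4 | none | yes | no device |
| 5 | none | no | no sessions |

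Only Groups 1 and 2 look alike to the patient: 2 × 12 = 24 of 60. The other 3 × 12 = 36 lack a component they can notice.

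**2. Which comparisons the hypotheses name.** The fNIRS hypothesis and the Discussion use the word alone, which is the Randomization section's label for Groups 3 and 4. The first hypothesis omits that word. No hypothesis names sham tDCS plus MT as comparator. Statistical methods gives a likelihood ratio test of all treatment and time-by-treatment coefficients and names no pairwise contrast.

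**3. What the stated sample size covers.** Stated inputs: f = 0.25, alpha 0.05, power 80%, five groups, three time points. Assumed, because not stated: correlation between time points 0.5 and no sphericity correction. For the group-by-time interaction:

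- noncentrality = f² × N × m / (1 − rho) = 0.0625 × 45 × 3 / 0.5 = 16.875
- degrees of freedom (5 − 1)(3 − 1) = 8 and (45 − 5)(3 − 1) = 80
- power = 0.81, which reproduces the stated 45
- dropout: 45 / 0.8 = 56.25, so 57, and 60 in equal groups of 12

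The calculation sizes the overall five-group interaction, not Group 1 versus Group 2.

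**4. Power of the sham-controlled contrast.** Two-sided t-test on final scores, 12 per arm, 22 degrees of freedom, noncentrality d × √(12/2). At d = 0.8 this is 0.8 × 2.449 = 1.96. The values of d are assumed.

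| Assumed d | Power |
|---|---|
| 0.5 | 22% |
| 0.8 | 47% |
| 1.0 | 65% |

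The effect detectable with 80% power is d = 1.20, or 1.41 with 9 completers per arm. Adjusting for baseline at an assumed correlation of 0.5 to 0.7 gives 58% to 75% at d = 0.8 and 27% to 38% at d = 0.5.

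**5. One team per arm (illustration only).** Take total variance as 1 and a team intraclass correlation ICC. The variance of an arm mean is ICC + (1 − ICC)/12, while the analysis assumes (1 − ICC)/12. The actual type I error is 2 × P(t₂₂ > 2.074 × √(assumed/actual)).

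| Assumed ICC | Assumed variance | Actual variance | Type I error |
|---|---|---|---|
| 0.02 | 0.0817 | 0.1017 | 0.076 |
| 0.05 | 0.0792 | 0.1292 | 0.119 |
| 0.10 | 0.0750 | 0.1750 | 0.188 |

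With one team per arm, no model can separate team from treatment.

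**The case against.** Several objections have force.

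- **No main contrast is fixed.** A reader might infer that the open arms were chosen in place of Group 1 versus Group 2. The article does not support that. Its omnibus test includes Group 2, the first hypothesis can be read to cover Group 2 as a music arm, Group 5 is in no hypothesis, and the ordering of contrasts may stand in an analysis plan that is not shown. What stands is narrower: Group 2 is never named as comparator, while two hypotheses use the names of Groups 3 and 4.
- **Open comparisons are partly unavoidable.** The aim is to beat each component, and no arm allows a blinded test of adding music. That is a reason to describe those comparisons accurately.
- **Assessor blinding is a real safeguard.** Two blinded psychiatrists rate cognition and symptoms, and nothing here refutes that. Expectancy may act through effort, but the article gives no basis for its size or for assuming that it passes in full into the MCCB difference, so no figure is put on it.
- **Team effects may be small.** The playlist, current and session length are fixed and timing is matched across Groups 1 to 4. The ICCs are assumptions. The article also does not say whether the Group 2 team's plan is labelled sham, although current only during the two ramps is a recognisable plan.
- **The principal investigator's checks are ordinary quality control.** Data collection and analysis staff are blinded, and the first unblinding shows only masked codes. No route to altered scores is shown. The arrangement is an avoidable weakness, not evidence of bias.

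**Conclusion.** The contradiction is established from the article alone: it claims blinding of all participants and a double-blind, sham-controlled design, yet sham control covers one contrast and 24 of 60 patients. This rests on no assumed figure and needs correcting, because it determines how a Group 1 versus Group 4 result could be described.

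The confounding of team with treatment also follows directly from the text and reaches Group 1 versus Group 2. Its size is unknown. The range of about 8% to 19% for type I error holds only under the assumed ICCs and 12 patients per arm.

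Two limits belong with the conclusion. Group 3 is open as to music but not necessarily as to active versus sham current. And Group 1 versus Group 2, though the only sham-controlled test, is weak at this size: about 47% power at an assumed d = 0.8.

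**What to change.** 1. Limit the participant-blinding claim to active versus sham tDCS in Groups 1 and 2. Describe comparisons with Groups 3, 4 and 5 as participant-unblinded and assessor-blinded.
2. Name Group 1 versus Group 2 as the sham-controlled test of adding tDCS to music, and state its low power at 12 per arm. State that adding music (Group 1 versus Group 3) has no blinded contrast in this design.
3. Where the device allows coded active and sham settings, have the same operators treat Groups 1 and 2. The article does not describe this device feature, so it must be checked. Operators may need to rotate, since sessions run in the same time period.
4. Keep the allocation key with the independent statistician until data lock, because the principal investigator has CRF access and checks CRFs weekly.

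Items 1, 2 and 4 are changes of wording and of task, and can still be made before data lock although recruitment began in December 2024. Item 3 can help only patients not yet treated. The cost is that fewer comparisons can be called double-blind and that coded settings must be arranged.
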